**Discussion:**

This is the first study to compare the changes in menstrual pain after three different interventions: the active intervention (AHP), the placebo intervention (APP), and a period of no intervention (WL). This three-arm randomized controlled trial (RCT) aims to investigate the relative contributions of the specific (AHP vs. APP) and non-specific (APP vs. WL) effects to the overall clinical effects of the active AHP on women with PDM. The scientific and rigorous methodology design of this trial should gather good evidence to assess the curative effects and safety of the AHP on PD. Moreover, the results of this study may provide evidence-based references for the treatment of menstrual pain in future.

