### Sample size calculation

A few scientific trials have investigated the biomechanical effects of acupoint plaster on PD; however, the research methodologies are not appropriate to reference the determination of sample size to this study. The article being used for our study, was from an acupuncture clinical report with the use of VAS scores [16]. Liu’s study reported that patients who received classical acupoint achieved a mean reduction of 36.1 in VAS after acupuncture; while patients who received non-acupoint treatment showed a worse score of 29.9. Therefore, the decrease in VAS score of the three groups was predicted to be 38, 29 and 26, respectively. Using a bilateral test with an alpha value of 5% and a power of 80%, standard deviation for each group was 20 mm. According to the calculation with PASS software (Version 11.0, NCSS, LLC. Kaysville, UT, USA) in a 1:1:1 ratio, the effect size is 0.2550 of 51 participants in each group. The sample size is also calculated using the following formula [58]:$$ n\kern0.5em =\kern0.5em 2{\left(\sigma \frac{z_{1-\alpha /\left(2\tau \right)}+{z}_{1-\beta }}{\mu_A-{\mu}_B}\right)}^2. $$

Allowing for a 15% dropout, the sample size was increased to 60 per group, making a total of 180.

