#### Methods of statistical analyses

Data analyses will be processed with SPSS 22.0 (SPSS Inc., Chicago, IL, USA) and supervised by a skilled statistician blinded to group allocation.

The Full Analysis Set (FAS) is for all participants who have been randomized in terms of the intention-to-treat (ITT), and the per-protocol analysis set (PPS) and is for the individuals who complete the trial and do not have significant protocol violations. On the basis of rule of the last-observation-carried-forward, missing values will be imputed. In order to evaluate therapeutic effect and safety, the FAS and PPS will be used simultaneously.

Categorical data, such as gender and medical history, will be tabulated with frequencies or percentages; and continuous data, such as age and disease course, will be reported as mean ± standard deviation (SD), or median. For the baseline variables, sociodemographic data and other basic indicators will be carried out using analysis of variance (ANOVA) and *χ*^2^. To compare variables before and after treatment in the same group, a paired *t* test will be used. Repeated measures analysis of variance (ANOVA) will be used to compare the intergroup differences among the three groups. Tests of ITT between the AHP and APP arms and between the APP and WL arms with respect to the change will based on time-intervention interactions in the mixed-effect models. A *P* value of less than 0.05 (two-sided) indicates a statistically significant difference, with 95% confidence intervals.

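### The stated 80% power belongs to a three-group omnibus F test; the two contrasts the trial sets out to answer have about 61% and 12% power, and the second printed formula does not give 51 per group

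*Protocol article*

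**What the plan says.** The section on sample size calculation assumes that "the decrease in VAS score of the three groups was predicted to be 38, 29 and 26, respectively", in the order herbal plaster (AHP), placebo plaster (APP) and waiting list (WL), and that the "standard deviation for each group was 20 mm". The design values are given as "Using a bilateral test with an alpha value of 5% and a power of 80" per cent. The PASS result is that "in a 1:1:1 ratio, the effect size is 0.2550 of 51 participants in each group". A two-mean formula follows, introduced by "The sample size is also calculated using the following formula [58"; it carries a term τ that divides alpha. Neither τ nor the pair A and B is defined, and no result is given. The final step is "Allowing for a 15% dropout, the sample size was increased to 60 per group, making a total of 180".

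The Discussion paragraph of the abstract says the three-arm trial "aims to investigate the relative contributions of the specific (AHP vs. APP) and non-specific (APP vs. WL) effects to the overall clinical effects", meaning those seen with the herbal plaster, and the main Discussion repeats this aim. The section on methods of statistical analyses plans "Tests of ITT between the AHP and APP arms and between the APP and WL arms with respect to the change", using time-by-intervention terms in mixed-effect models, and sets significance at P < 0.05. It also plans a repeated-measures ANOVA over the three groups.

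**The concern.** The sample size section never says which test its 80% refers to. An effect size of 0.2550 with equal n in three groups points to an omnibus F test, which asks only whether some arm differs from another. That test cannot separate a specific effect from a non-specific one, and separating them is the stated reason for having three arms. The omnibus test also draws on the 12 mm AHP vs WL gap, which is not one of the two named contrasts. The second formula then gives the impression that a pairwise calculation supports the same n.

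If so, a reader would credit the efficacy comparison (AHP vs APP) with a 20% risk of missing the assumed effect when the risk is nearer 39%. For APP vs WL, a non-significant result would be the expected outcome even if the assumed 3 mm were true, and could easily be taken to mean that there is no placebo effect.

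**Working it through.** **Inputs**, all from the section on sample size calculation: mean VAS decreases 38, 29 and 26 mm; SD 20 mm; two-sided alpha 0.05; power 0.80; 51 per group before and 60 after a 15% dropout allowance. Pairwise differences: AHP vs APP 38 − 29 = 9; APP vs WL 29 − 26 = 3; AHP vs WL 38 − 26 = 12 mm.

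**Step 1. Reproduce the plan's figure.** The grand mean is 31 and the deviations are 7, −2 and −5.

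- Standard deviation of the means = √[(49 + 4 + 25)/3] = √26 = 5.099
- Cohen's f = 5.099/20 = 0.2550, as printed
- Noncentrality at 51 per group = 153 × 26/400 = 9.945
- Noncentral F power: 79.6% at n = 50, 80.5% at n = 51
- Dropout: 51/0.85 = 60 per group, 180 in total

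So 0.2550 and 51 are the one-way, three-group F test result, and the dropout step is correct.

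**Step 2. What drives the omnibus power.** The sum of squared deviations (78) equals one third of the sum of squared pairwise differences: (81 + 9 + 144)/3 = 78. AHP vs WL supplies 144/234 = 62% of it, AHP vs APP 81/234 = 35%, and APP vs WL 9/234 = 4%.

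**Step 3. Power of each contrast.** Two-sample t test on one change score, SD 20, noncentrality δ/(20√(2/n)), two-sided:

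| Contrast | δ (mm) | n = 51, α = 0.05 | n = 51, α = 0.025 | n = 60, α = 0.05 |
|---|---|---|---|---|
| AHP vs APP | 9 | 61.4% | 50% | 68.6% |
| APP vs WL | 3 | 11.7% | 7% | 12.9% |
| AHP vs WL | 12 | 85.1% | 77% | 90.3% |

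The α = 0.025 column splits alpha over the two named tests. By the normal approximation, the difference detectable with 80% power at n = 51 is 20 × √(2/51) × (1.960 + 0.842) = 11.1 mm, against the assumed 9 and 3 mm.

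**Step 4. The printed formula.** n = 2[σ(z₁₋α/(2τ) + z₁₋β)/(μA − μB)]², with z₁₋β = 0.842 and z₁₋α/(2τ) = 1.960, 2.241 and 2.394 for τ = 1, 2 and 3. For 9 mm and τ = 1: 2 × (20 × 2.802/9)² = 77.5, so 78. In full, rounded up:

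| Contrast | τ = 1 | τ = 2 | τ = 3 |
|---|---|---|---|
| AHP vs APP (9 mm) | 78 | 94 | 104 |
| APP vs WL (3 mm) | 698 | 845 | 931 |
| AHP vs WL (12 mm) | 44 | 53 | 59 |

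No entry is 51. The closest is 53, for AHP vs WL with τ = 2, which is not one of the two named contrasts.

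**The case against.** Four points deserve weight.

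- **The figures in the section are correct for the F test, and a three-group ANOVA is planned.** True. The fault is not a slip in 0.2550, 51 or 60. It is that only one of the two planned analyses is powered, and that one does not answer the stated questions.
- **The contrasts would use the full analysis set, hence about 60 per arm.** The full analysis set is all randomised participants with last observation carried forward, so the n = 60 values are relevant and should be shown. At 69% and 13% they still fall short of 80%.
- **The planned test is a mixed model over several cycles, not a t test on one change score.** This stands as a qualification. The protocol's own calculation uses a single SD of 20 and states no correlation. If one assumes that the variance falls by a factor (1 − ρ²) with ρ from 0.3 to 0.7, power at 51 per arm becomes about 66% to 89% for 9 mm but only 12% to 18% for 3 mm. AHP vs APP could therefore reach 80% with a strong correlation; APP vs WL could not.
- **The formula has no stated result, so it cannot be said to disagree.** It is literally true that no number is attached. But the word used to introduce it implies agreement with 51, and for both named contrasts the result is far higher. The near match of 53 should be acknowledged.

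The main Discussion calls this a pilot study, and confidence intervals are already planned. Neither changes what the stated 80% refers to.

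**Conclusion.** The point holds. The 80% is the power of an omnibus three-group F test and does not carry over to either contrast the trial names. On the protocol's own means and SD, with unadjusted two-sided 5% tests of a single change score, AHP vs APP has about 61% power at 51 evaluable per arm (69% at 60) and APP vs WL about 12% (13% at 60). The AHP vs APP figure could improve under a repeated-measures model, by an amount the document does not allow one to fix. The APP vs WL shortfall stays below about 20% across the correlations examined. The two-mean formula does not support 51 for either named contrast, and gives exactly 51 for no pair with τ from 1 to 3. This must be corrected, because the section credits the design with a property it lacks for its own questions.

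**What to change.** Keep N = 180 and restate the power:

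1. Say that 80% (80.5% at 51 per group) is the power of the three-group omnibus F test.
2. Give power for each contrast at both sample sizes: AHP vs APP about 61% (51 evaluable) and 69% (60); APP vs WL about 12% and 13%; AHP vs WL about 85% and 90%. State that these are two-sided 5% t tests on a change score with SD 20, without multiplicity adjustment. Any gain claimed for the mixed model should come with its assumed correlation.
3. Delete the statement that the two-mean formula was also used, or define τ and the pair and print the results (78/94/104 for AHP vs APP; 698/845/931 for APP vs WL).
4. As an optional further step, declare APP vs WL an estimation objective, reported as a difference with its 95% confidence interval, and state that a non-significant result will not be read as absence of a non-specific effect.

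Items 1 to 3 are wording only: no extra participants, but a less favourable stated power. Item 4 changes the status of a planned hypothesis test and should be recorded as such.

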### Statistical analysis plan

#### Data integrity

All participants are assessed at run-in period and at the first, second, third, fourth, fifth and sixth menstrual cycles after recruitment. A well-trained assessor, who is blinded to the treatment assignment, will collect clinical data using CRF files at each visit. Another two pre-trained data managers will verify and cross-check the CRFs, for the sake of ensuring reliability and accuracy of the data. If there are any queries in the CRFs, the results will be sent to the third investigator for resolution. Data managers will also be responsible for administration, coordination and monitoring (including Excel spread sheet-set up, data entry, coding and query management). Any incomplete data will be coded as unknown, missing or not applicable, and all data will be anonymously extracted to keep the identities of patients confidential. Results of the analysis must not be released with individual identification of the subject until the Excel spread sheet is closed.

#### Methods of statistical analyses

Data analyses will be processed with SPSS 22.0 (SPSS Inc., Chicago, IL, USA) and supervised by a skilled statistician blinded to group allocation.

The Full Analysis Set (FAS) is for all participants who have been randomized in terms of the intention-to-treat (ITT), and the per-protocol analysis set (PPS) and is for the individuals who complete the trial and do not have significant protocol violations. On the basis of rule of the last-observation-carried-forward, missing values will be imputed. In order to evaluate therapeutic effect and safety, the FAS and PPS will be used simultaneously.

Categorical data, such as gender and medical history, will be tabulated with frequencies or percentages; and continuous data, such as age and disease course, will be reported as mean ± standard deviation (SD), or median. For the baseline variables, sociodemographic data and other basic indicators will be carried out using analysis of variance (ANOVA) and *χ*^2^. To compare variables before and after treatment in the same group, a paired *t* test will be used. Repeated measures analysis of variance (ANOVA) will be used to compare the intergroup differences among the three groups. Tests of ITT between the AHP and APP arms and between the APP and WL arms with respect to the change will based on time-intervention interactions in the mixed-effect models. A *P* value of less than 0.05 (two-sided) indicates a statistically significant difference, with 95% confidence intervals.

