## Methods/design

### Study design

This proposed study is a single-centered, randomized, placebo-controlled trial which was devised following the Consolidated Standards of Reporting Trials (CONSORT) Statement recommendations [40] and the Standardized Protocol Items: Recommendations for Interventional Trials (SPIRIT) guidelines Additional file 1 [41]. Ethical approval has been obtained from the Institutional Review Board (IRB) of the Teaching Hospital of Chengdu University of Traditional Chinese Medicine (Approval No. 2016KL–003). We registered the study on the Chinese Clinical Trial Registry (Registration No. ChiCTR-IOR-16008701) in 2016.

The study will take place in the 3rd Affiliated Hospital of Chengdu University of TCM. During a run-in period of three menstrual cycles prior to randomization, the patients will be required to complete a Dysmenorrhea Diary (DD) and record related symptom scores every month to establish an individualized baseline score. A total of 180 subjects meeting the including criteria will be allocated randomly to three research groups that include one experimental group of the AHP and two control groups of the acupoint placebo plaster (APP) group and the waiting-list WL group. After randomization, subjects in the AHP and APP groups will receive treatments for another three menstrual cycles. Follow-up assessments through telephone calls or social media smartphone application will be processed for the last period of three menstrual cycles until the completion of study. Altogether it takes 9 months of three stages with three period cycles in each session. (See Fig. 1 for the study flowchart, and Fig. 2 for the assessment schedule).

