### Outcome measurements

#### Primary outcome

The primary outcome will be pain intensity reduction measured by the Visual Analog Scale (VAS). The severity of menstrual pain will be estimated using the VAS graded from 0 mm to 100 mm, indicating an absence of pain to the most serious pain imaginable [49].

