#### Time points of outcome measurements

The VAS, CMSS, SF-12 and DD will be recorded at baseline and at every menstrual cycle throughout the treatment and the follow-up periods. The PGIC will be measured at the first, second, third, fourth, fifth and sixth menstrual cycles after inclusion.

We will estimate the expectation of participants to determine whether their expectations affected the outcomes by using the Credibility Expectancy Questionnaire (CEQ) [53, 54] at the baseline and the first to the third menstrual cycle before receiving treatment. In the proposed study, the questionnaire will be used to control for placebo effects, which are expected to be relatively high for light-therapy studies [54]. Blinding will be assessed by asking participants what group they thought they were in (AHP group or APP group, or “don’t know”) at the end of trial, and why they believed that they were in that group.

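### Last observation carried forward is the stated rule for all missing values although the planned mixed-effects model needs no imputation; where pain is still changing it can bias both contrasts, in either direction

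*Protocol article*

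**What the plan says.** Under Methods of statistical analyses, the protocol article fixes one rule: "On the basis of rule of the last-observation-carried-forward, missing values will be imputed". The rule is not limited to an outcome, a period or an analysis set, and it is not given a sensitivity role.

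The same section plans two between-group analyses. For the three arms together: "Repeated measures analysis of variance (ANOVA) will be used to compare the intergroup differences among the three groups". For AHP against APP and APP against WL, intention-to-treat tests "with respect to the change will based on time-intervention interactions in the mixed-effect models". The full analysis set contains all randomised women. It is analysed alongside a per-protocol set restricted to women who complete the trial without significant violations.

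Treatment lasts three cycles after randomisation, and three cycles without treatment follow: "Follow-up assessments through telephone calls or social media smartphone application will be processed for the last period of three menstrual cycles" (Study design). The VAS and the other scales except the PGIC "will be recorded at baseline and at every menstrual cycle throughout the treatment and the follow-up periods" (Time points of outcome measurements).

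Sample size calculation predicts VAS decreases of 38, 29 and 26 mm for the three groups with an SD of 20 mm. On loss it says only: "Allowing for a 15% dropout, the sample size was increased to 60 per group".

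**The concern.** Carrying a value forward is right on average only if pain would not have changed after the last record. The plan itself expects large changes from baseline, including 26 mm in untreated women, and treatment ends halfway through the six assessed cycles. A woman lost early may have a partial response carried into cycle 3 and beyond. A woman lost at the end of treatment has an on-treatment score entered as follow-up data. The filled values are then analysed as if recorded, so the standard errors take no account of the imputation.

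The time-by-intervention term that carries both contrasts depends directly on how scores move across cycles, which is what the rule freezes. The mixed-effects model does not need it, so the rule adds a stronger assumption and gains nothing for those contrasts. At stake are the estimated specific effect (AHP-APP), the estimated non-specific effect (APP-WL) and any statement about durability after treatment.

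**Working it through.** **The plan's own figure.** The mean of 38, 29 and 26 is 31. The effect size is √[(7² + 2² + 5²)/3]/20 = √26/20 = 0.2550, as stated. One-way ANOVA power at two-sided 5% is 0.796 with 50 per group and 0.805 with 51, so 51 per group reproduces. Then 51/0.85 = 60 per group, 180 in all. At 15% loss, about 9 of 60 women per arm (27 of 180) would have carried-forward values.

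**When the rule biases.** If a fraction d of an arm is lost after cycle l and would have followed that arm's mean course, the error in the arm mean at cycle t is d × (mean at l − mean at t). The error in a contrast is the difference between two such terms. It is zero if neither arm changes after l, whatever the dropout. It can be non-zero with equal dropout if the arms change by different amounts.

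**Loss after cycle 1, effect then maintained.** Inputs from the article: decreases of 38, 29 and 26 mm and 15% overall loss. Assumed: one third of the final reduction is reached at cycle 1, and the loss splits by arm as shown. The carried-forward mean is R × (1 − d × 2/3).

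| Contrast | Loss by arm | True (mm) | Carried forward (mm) |
|---|---|---|---|
| AHP-APP | 15% / 15% | 9 | 34.20 − 26.10 = 8.1 |
| AHP-APP | 20% / 10% | 9 | 32.93 − 27.07 = 5.9 |
| AHP-APP | 10% / 20% | 9 | 35.47 − 25.13 = 10.3 |
| APP-WL | 15% / 15% | 3 | 26.10 − 23.40 = 2.7 |
| APP-WL | 10% / 20% | 3 | 27.07 − 22.53 = 4.5 |
| APP-WL, WL at 26 mm by cycle 1 | 10% / 20% | 3 | 27.07 − 26.00 = 1.1 |

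**Range over the one-third assumption.** Let s be the share of the final reduction present in the last record. The AHP-APP result is 9 − 4.7(1 − s) at 20%/10%, 9 + 2.0(1 − s) at 10%/20%, and 9 − 1.35(1 − s) at 15%/15%. From s = 0 (baseline carried) to s = 1 (full response already reached), these run from 4.3 to 9.0, from 11.0 to 9.0, and from 7.65 to 9.0 mm.

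**Follow-up, with all reductions assumed to halve by cycle 6.** The true AHP-APP difference at cycle 6 is 19 − 14.5 = 4.5 mm, and the true AHP reduction is 19.0 mm.

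- 25% AHP / 10% APP lost after cycle 3: AHP 0.75 × 19 + 0.25 × 38 = 23.75; APP 0.90 × 14.5 + 0.10 × 29 = 15.95; difference 7.8 mm.
- 10% / 25% lost after cycle 3: 20.90 − 18.13 = 2.8 mm.
- 15% / 15% lost after cycle 3: 21.85 − 16.68 = 5.2 mm.
- 25% of AHP lost after cycle 1: AHP 0.75 × 19 + 0.25 × 12.67 = 17.4 mm, so persistence is understated.

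**Comparison with the model on observed data.** A simulation used 60 women per arm, 150 runs, within-person correlation 0.5 and dropout random within arm, with 25% of AHP and 10% of APP lost. For loss after cycle 1 with the effect maintained, carrying forward gave 5.1 mm at cycle 3 (expectation 4.6) against a true 9.0. A random-intercept mixed model without imputation gave 9.3 (Monte Carlo SE 0.34). For loss after cycle 3 with waning, the figures at cycle 6 were 7.9 and 4.7 (SE 0.29) against a true 4.5.

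**The case against.** **Size and direction.** The article does not give what is needed to size the error. It states one mean decrease per arm, not a course over cycles, and one overall dropout figure. If the reductions are reached by cycle 1 and held, the bias is zero. Entry requires a VAS of at least 40 mm, so untreated women may improve early through regression to the mean; the APP-WL error then changes sign. At equal 15% loss the AHP-APP error is 0.9 mm against an SD of 20 mm. All of this stands, and the figures are scenarios.

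**Differential loss.** Unequal dropout is an inference. WL women know their allocation, and skin reactions may occur with plasters. But a reaction requires removal of the plaster, not withdrawal from the trial; women with mild or moderate events remain under follow-up; WL women are offered free treatment at completion; and follow-up is remote. That stands too.

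**Stronger readings.** A reader might infer that any difference in dropout between arms biases the contrasts, or that persistence will be overstated. The documents support neither. Bias requires change after the last record, whether or not dropout differs. Overstated persistence requires late loss and a return of pain, and the article predicts neither.

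**Other defences.** Repeated measures ANOVA in its standard form needs complete series, which may be why a filling rule was written. That is a reason to settle that analysis too, not to impute for the mixed model. The per-protocol set offers little check, because it selects on completion. The mixed model is not immune either: the simulation made dropout random within arm, which favours it. Finally, sensitivity analyses may sit in an analysis plan that is not shown; their absence from the article adds no weight here.

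**Conclusion.** The concern holds as a statement about what the rule can do. Last observation carried forward is the stated rule for all missing values, alongside a model that does not need it. It can bias both contrasts in either direction and can misstate persistence, and it treats filled values as observed.

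With loss after cycle 1 at one third of the final reduction, a true 9 mm AHP-APP difference becomes 8.1 mm at equal 15% loss and lies between 5.9 and 10.3 mm under 2:1 loss. A true 3 mm APP-WL difference becomes 4.5 or 1.1 mm depending on how fast untreated women improve. It is unbiased if nothing changes after the last record. The course over cycles and the timing and split of loss are assumptions. The plan should be changed, but with the size unknown and the remedy confined to the analysis, this does not rank among the defects that must be resolved before the trial can proceed.

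**What to change.** - Remove last observation carried forward from the main analysis.
- Make the mixed-effects model, fitted to all observed cycles of all randomised women under missing-at-random, the primary analysis.
- Use the same model for the three-group comparison in place of the repeated measures ANOVA on filled data. If the rule is simply deleted, the ANOVA falls back on completers.
- Add one missing-not-at-random sensitivity analysis, such as delta-adjusted or reference-based multiple imputation, with the delta or reference arm fixed before unblinding.
- Keep last observation carried forward at most as a labelled sensitivity analysis.

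The cost is a change of analysis wording and a little more analysis work. The sample size stays at 51 evaluable and 60 randomised per group. The article reports recruitment as ongoing; on that status the change can be made before allocation is revealed.

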In the AHP group, the standard operating procedures (SOP) are listed as follows:Prepare the herbal materials: SFZYT includes *Angelicae sinensis Radix* (*danggui*), Rhizoma (*chuanxiong*), *Paeoniae Radix rubra* (*chishao*), *Cinnamomi cortex* (*rougui*), *Foeniculi fructus* (*xiaohuixiang*), *Zingiberis rhizoma (ganjiang*), Myrrha (*moyao*), *Trogopterus dung* (*wulingzhi*), Typhae Pollen (*puhuang*) and *Corydalis rhizoma* (*yanhusuo*). The ingredients of this formula are mixed in a weight ratio of 3: 1: 2: 1: 0.5: 2: 1: 3: 1: 1 and then the raw materials ground into fine powder (under 75 μm diameter) using a special Chinese medicinal crop powder mixer (manufactured by Royalstar Co., Ltd., Hefei, China)Add the liquid base: place the mixed herbal powder into a container, add honey and stir well to make a thick herbal pasteAdd the sticky plaster: put 10 g of the herbal paste onto a medical sticky plaster. Then apply the plaster over the acupoints. The sticky plasters are sized 5 × 5 cm^2^ with a 0.8-cm radius in the middle of which is placed the host herbal paste. The rest of the sticky plaster carries no herbal paste, which makes it adhere to the skin over the acupointsTreatment procedures: locate the acupoints, disinfect the skin, and attach the plaster on the skin over the acupoints. The plasters will be left on the skin for 4–8 h depending on each patient’s individual response because it must be removed immediately should any allergic reaction occur, which may be described by patients as a burning sensation, severe itchiness, blisters, pruritus or rash on the local skin. A total of nine sessions will be performed during the three menstrual cycles, the treatment starts 1 week prior to the menstruation, with one 6–8-h treatment three times per week, according to the subject’s estimated dates

For the APP group, the placebo paste is made of buckwheat flour without any herbal medicines; however is still mixed with honey to maintain a similar appearance to the AHP (Fig. 2c and d) so that the plasters used in these two experimental groups are undistinguishable to patients and practitioners. Moreover, the only variable between the AHP group and the APP group is the ingredients of paste. In order to reduce the bias caused by performance, all the rest of the clinical procedures remain the same.

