### Safety evaluation

Clinical adverse events (AEs) will be recorded throughout the study and graded using the National Cancer Institute Common Terminology Criteria for Adverse Events (CTCAE) version 4 [55]. According to previous randomized controlled trials (RCTs) [56, 57], the AHP may cause potential adverse events of itchiness, allergic responses of the skin or the whole body, local infections and other mild side effects. Any unexpected symptoms or signs during the treatment must be documented regardless of their relation to the study intervention. All details of related and unexpected AEs, such as time of occurrence, severity of AE, and suspected causes, will be recorded on Case Report Forms (CRFs). Participants with mild and moderate AEs will receive symptomatic treatment and will be closely followed up by the research team. Severe AEs will be reported to the Research Ethics Committee within 48 h.

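### The per-protocol set is used for safety alongside the full set, so women who withdraw because of a reaction drop out of one of two safety rates, and neither set is ranked.

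*Protocol article*

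**What the plan says.** The section Methods of statistical analyses in the protocol article defines two analysis sets. For the first: "The Full Analysis Set (FAS) is for all participants who have been randomized in terms of the intention-to-treat (ITT"). The second, the PPS, "is for the individuals who complete the trial and do not have significant protocol violations". It then assigns both sets to both purposes: "In order to evaluate therapeutic effect and safety, the FAS and PPS will be used simultaneously". No separate safety set is named, and this sentence does not say which set leads.

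Later in the same section, two pairwise comparisons are linked to intention-to-treat: "Tests of ITT between the AHP and APP arms and between the APP and WL arms with respect to the change", by way of time-intervention interactions in mixed-effect models. The repeated measures ANOVA across the three groups and the within-group paired t tests are described without any analysis set.

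On harms, Safety evaluation says "the AHP may cause potential adverse events of itchiness, allergic responses of the skin or the whole body, local infections and other mild side effects", and "Clinical adverse events (AEs) will be recorded throughout the study". The operating procedure under Interventions says of the plaster that "it must be removed immediately should any allergic reaction occur".

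**The concern.** A set restricted to completers is a poor basis for a rate of adverse events when the event itself can cause withdrawal. The harms expected here are local and systemic reactions to what is applied to the skin, which are plausible reasons to leave. In the PPS, the adverse-event rate is a rate among women who tolerated the plaster well enough to finish.

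The herbal and placebo plasters are meant to differ only in the paste. If reactions to the herbal ingredients lead to more withdrawals than reactions to the buckwheat paste, the PPS comparison of harms between those arms is distorted in favour of the herbal plaster. The documents do not show that this will happen, but the plan leaves it open. Safety is a stated aim of the trial, and a report could present either rate.

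For efficacy, the sentence leaves unstated which set governs if the two disagree in the analyses that are not tied to intention-to-treat.

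**Working it through.** The plan gives no reaction, withdrawal or exclusion rate by arm, so there is no figure of its own to reproduce on this point. The check has four parts.

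**1. Which women each set keeps.**
- FAS: every randomised woman. A reactor who withdraws stays in, with her event.
- PPS: completers without significant violations. A reactor who withdraws from the trial is out, with her event.
- Events are recorded throughout the study, so they are available for the FAS count.

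**2. Size of the gap between the two safety rates (assumed counts).** Let N = 60 in the herbal-plaster arm (from Sample size calculation), R = women who react and W = reactors who withdraw, with nobody else excluded.
- FAS rate = R / N
- PPS rate = (R − W) / (N − W)

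With R = 6 and W = 4: FAS 6/60 = 10.0%; PPS (6 − 4)/(60 − 4) = 2/56 = 3.6%.

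Expected values over a range of assumptions:

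| Reaction rate | FAS | PPS, 0% of reactors withdraw | 25% | 50% | 100% |
|---|---|---|---|---|---|
| 10% | 6/60 = 10.0% | 10.0% | 4.5/58.5 = 7.7% | 3/57 = 5.3% | 0/54 = 0% |
| 20% | 12/60 = 20.0% | 20.0% | 9/57 = 15.8% | 6/54 = 11.1% | 0/48 = 0% |

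The planned 15% dropout is 0.15 × 60 = 9 women per arm. If 4 of those 9 are reactors, and 6 women react in all, the PPS rate is 2/51 = 3.9%. The direction is not guaranteed. If no reactor leaves but 10% of the 54 non-reactors do, the PPS rate is 6/(6 + 48.6) = 6/54.6 = 11.0%.

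**3. Efficacy.** Setting the sentences side by side:
- mixed-model contrasts, herbal vs placebo plaster and placebo plaster vs waiting list: tied to intention-to-treat, hence to the FAS;
- three-group repeated measures ANOVA: no set named;
- paired t tests within group: no set named.

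If, contrary to anything stated, a significant result in either set counted, the type I error of one contrast would exceed 0.05. Take the correlation between the two test statistics as the square root of the share of the FAS kept in the PPS. The error is then about 0.060, 0.068 or 0.076 when the PPS keeps 95%, 85% or 70%.

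**4. Sample size, to see whether the fix touches it.** The predicted decreases are 38, 29 and 26 (mean 31), with SD 20.
- SD of means = √[(7² + 2² + 5²)/3] = √26 = 5.099; effect size = 5.099/20 = 0.2550, as stated.
- The three-group F test at two-sided 5% has power 0.796 with 50 per group and 0.805 with 51, so 51 per group.
- 51/0.85 = 60 per group, and 3 × 60 = 180.

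All these figures reproduce, and none depends on the analysis-set sentence.

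**The case against.** The strongest reply is that safety is evaluated in the FAS as well. Every randomised woman is in that set, and the 10.0% in the illustration is a figure the protocol already plans to produce; the 3.6% would stand beside it. This is correct. A reader might infer that safety rests on the PPS alone, or that reactions are lost from the trial's safety evaluation. The documents do not support either. What remains is that a second rate, open to bias, is planned with no statement of which one prevails.

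A reader might also infer that any woman whose plaster comes off early because of a reaction leaves the PPS. The text does not establish this. Removal on a reaction is part of the written procedure, so it is not evidently a violation, and finishing the trial is not the same as wearing every plaster for the full time. The procedure gives wear time as both 4–8 h and 6–8 h, passages that must be reconciled, but neither says that a short session excludes a woman. Withdrawal from the trial is the only secure route out of the PPS.

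A third tempting reading is that the two sets have equal rank for efficacy, so that a result in either suffices. That is an inference from the word simultaneously. No such rule is stated, and the two pairwise contrasts are tied to intention-to-treat. The type I error figures above are therefore conditional on a rule the protocol does not contain. The link does not extend to the ANOVA or the paired t tests, so the gap there is real.

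Finally, both plasters share the honey base and the same procedures, and no arm-specific reaction rate is given. Differential bias between arms is possible but not shown.

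**Conclusion.** The point holds in a limited form. The protocol states, rather than merely leaves open, that safety will be evaluated in a completer set. In that set, a woman who withdraws because of a reaction takes her event with her. This is not something left to a later analysis plan.

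The size cannot be fixed from the documents. With nobody else excluded, the understatement in the PPS runs from none (no reactor withdraws) to complete (all do). The illustration of 10.0% against 3.6% rests on assumed counts of 6 reactors and 4 withdrawals. The FAS safety count is unaffected in every case.

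The efficacy half is weaker: the order of the sets is unstated for the three-group ANOVA and the paired t tests, while the named pairwise contrasts already point to the FAS. The change is worth making because it removes a source of bias at almost no cost. It does not call the design or the sample size into question.

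**What to change.** Amend the analysis-set sentence in Methods of statistical analyses:

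- **Safety:** drop the PPS. Report adverse events in all women who received at least one plaster, grouped by the plaster received. Show all randomised waiting-list women separately, since they receive no plaster during the study.
- **Efficacy:** name the FAS as the primary set for all comparisons, including the repeated measures ANOVA and the paired t tests. Keep the PPS as a supportive sensitivity analysis that cannot carry a claim alone.

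The cost is a slightly longer analysis section. The figures of 51 per group, 60 per group and 180 in total stay as they are, and no extra data are needed because adverse events are already recorded throughout. The article gives recruitment as ongoing, so at that stage the change could still be made before allocation is revealed.
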